## Abstract

**Background:**

Knee arthroplasty is being increasingly performed, and also more often in a younger patient population (<65 years of age). Up to 20 % of patients remain dissatisfied after knee arthroplasty, despite the apparent technical success of the operation. Recent studies suggest that the fulfilment of patients’ expectations plays an important role in achieving satisfaction. Thus, addressing preoperative expectations more explicitly might improve patient satisfaction. The primary aim of the present study is to investigate the effect of a multidisciplinary, goal attained and individualized rehabilitation on satisfaction of activities of younger patients (<65 years) after knee arthroplasty.

**Methods/design:**

A single-centre randomized controlled trial will be conducted. In total, 120 patients (<65 years of age) with knee osteoarthritis who will undergo knee arthroplasty, will be randomly allocated to either goal attainment scaling rehabilitation or usual care rehabilitation. Goal attainment scaling rehabilitation includes drafting individually set rehabilitation goals preoperatively and measuring progress of rehabilitation on a six-point scale (-3 to +2). The primary outcome is patient satisfaction concerning activities in daily life, work and leisure time, including sports. Secondary outcome measures include KOOS, OKS, SQUASH and WORQ questionnaires and activity objectively measured with the Activ8® activity monitor.

**Discussion:**

The findings of this study will help to elucidate whether goal attainment scaling is an effective rehabilitation method for achieving higher levels of patient satisfaction, with a focus on activities, in younger patients after knee arthroplasty.

**Trial registration:**

This trial is since June 15^th^ 2015 registered at the Dutch Trial Register: NTR5251.

## Background

Osteoarthritis (OA) is a common chronic disease causing pain and disability among adults. In particular, the incidence of knee OA is high [1]. In the Netherlands, 594,000 persons suffer from knee OA [2]. Due to several external factors, such as aging of the population, epidemic obesity and secondary post-traumatic joint OA mainly caused by sports injuries, the prevalence of knee OA is expected to increase drastically in the Western world. At the same time, knee OA patients are becoming younger [3, 4].

Knee arthroplasty (KA), both total knee arthroplasty (TKA) and unicondylar knee arthroplasty (UKA), has proven to be a reliable form of treatment to relieve pain, improve function and enhance health-related quality of life [1]. Following the increasing prevalence of knee OA, the demand for KA is expected to rise worldwide [5]. In the Netherlands for example, an increase of 297 % of KAs from 2005 to 2030 is projected, with up to 57,900 KAs performed annually by 2030 [6]. Despite the aforementioned benefits of KA, 17–20 % of patients remain dissatisfied after surgery [7, 8]. In most of these cases, no implant-related mechanical failure can be found. The younger group of patients appears to expect to be more active and be able to perform more diverse activities after KA [3, 4]. These high preoperative expectations itself do not predict satisfaction after joint replacement [3], but *fulfilment* of these patient expectations clearly seems to play an important role in patient satisfaction [8, 9]. Current described percentages of fulfilment of expectations after KA range from 100 % satisfaction regarding knee pain alleviation to only about 20 % concerning the ability to participate in sports and leisure activities [8]. Although younger and more active patients may have higher expectations regarding activities, the expectations across patients vary highly for daily life, work and leisure time [10]. Patients expect to be able to return to work, but a recent study showed that the number of patients returning to work after KA is limited (<70 %) [11]. Concerning leisure time activities, a recent systematic review showed that return to intermediate- to high-impact sports is actually possible, and even more likely after UKA than after total knee arthroplasty (TKA) [12]. However, the literature suggests that patients often do not actually participate in functional levels of sports after KA [13]. Kersten et al. described that almost half of KA patients did not meet health-enhancing physical activity guidelines, and they were less active as a normative group [14].

Although the provision of postoperative physical therapy is almost universal, rehabilitation is the most understudied area concerning KA [15]. While short-term improvements of functional results with physiotherapy (PT) and exercise therapy after KA are shown in a recent systematic review, several aspects concerning rehabilitation after KA are unclear [16]. Recent surveys among physiotherapists showed that currently a great variety of PT methods is being used to attain patient goals in rehabilitation after KA [15, 17].

Considering the diverse expectations of this younger patient population on the one hand, and the importance of PT as part of rehabilitation on the other hand, the primary aim of the present study is to evaluate the effect of a multidisciplinary, goal attained and individualized rehabilitation on satisfaction of activities in daily life, work and leisure time including sports of younger patients (<65 years) after KA. The hypothesis is that multidisciplinary, goal attained and individualized rehabilitation, where patients’ goals are explicitly established and the feasibility of these goals is discussed and evaluated preoperatively, will result in higher patient satisfaction concerning these three domains compared to usual care physiotherapy rehabilitation.

## Methods/design

### CONSORT

In the description of our study design, we follow the Consolidated Standards of Reporting Trials (CONSORT statement) [18].

### Ethical principles

The study will be conducted according to the principles of the Declaration of Helsinki (59th World Medical Association General Assembly, Seoul, October 2008) and in accordance with the Medical Research Involving Human Subjects Act (WMO). Ethical approval has been received from the Medical Research Ethics Committee of the Academic Medical Center (AMC) Amsterdam. Patients will not be exposed to any potentially harmful procedures or therapies. No additional risks or discomfort are expected compared to standard rehabilitation. We only ask patients to fill in additional questionnaires preoperatively, after 3 months, after 6 months and after 1 year. This will take approximately 30 – 45 min. The online questionnaires can be completed at home at a convenient moment. In this way, we hope to minimize the extra burden for patients. There is no direct (financial) incentive for patients to participate in this trial. Patients’ motivation derives from the possible identification of a new treatment method that might benefit all future KA patients.

### Study design

The goAl attainment sCaling for knee arThroplasty In yOunger patieNts (ACTION) trial is a single-centre randomized controlled trial. Participants will be assigned to two groups: Usual care physiotherapy rehabilitation versus Goal Attainment Scaling (GAS) rehabilitation after KA. Figure 1 shows the CONSORT flow diagram of the ACTION trial.

**Fig. 1 Fig1:**
[figure not shown]
CONSORT Flow Diagram ACTION trial

### Study population

Patients that meet the following inclusion criteria are eligible for enrolment in this study:Patients < 65 years of ageDebilitating knee osteoarthritis with an indication for KA, but not yet operatedCurrently participating in a job (either paid or voluntary)Able to perform usual rehabilitation care

If any of the following criteria apply, patients will be excluded:Cognitive or mental impairmentNo adequate levels of reading and writing the Dutch languageAny disabling condition apart from knee osteoarthritis that restricts patients from performing their normal activities (e.g. pulmonary or cardiac disease, systemic inflammatory disease or pre-existing arthroplasty of hip or contralateral knee)

### Sample size

The primary outcome measure is a Visual Analogue Scale (VAS) for satisfaction regarding activities in daily life, work and leisure time, including sports. According to Singer et al. we use a minimal clinical relevant difference of ten points on a VAS scale from 0 to 100 with standard deviation of 15 [19]. Currently, data concerning how younger patients score satisfaction regarding activities in daily life, work and leisure time after KA are lacking. The best prediction can be extracted from the study of Kievit et al., in which young patients participating in a paid job with usual care after a KA scored a mean VAS score of 62 out of 100 points regarding work capacity [11]. According to these data, an intervention group has to score at least 72 (out of 100) points. Calculating with a power of 90 %, two-tailed testing with a *p*-value of 0.05, and standard deviation of 15 results in a minimum of 98 participants, 49 in the intervention group and 49 in the control group (nQuery Advisor® version 7.0). To adjust for 15 % dropouts over the 12 months follow-up period, 120 (60 per group) participants need to be included. It is expected that three patients per week can be included from the three locations of our hospital, so the inclusion period will cover approximately 40 weeks.

### Intervention

With patients wanting to participate in a great variety of activities postoperatively, standardized measurement tools do not always suffice in measuring what is relevant for the individual patient. GAS is a scoring method that measures the extent to which a patient’s individual goals are achieved by registering these goals on personal scales [20–22]. We will use the quality appraisal criteria for adequate scientific use of GAS scales that were recently suggested by Krasny-Pacini et al. [21] In our study, each goal is rated on a 6-point scale, ranging from -3 up to +2. The current situation is defined as -2 and the achievable goal for the patient after rehabilitation is marked as 0. A decline in performance is rated -3 and improvements are registered as -1, 0, +1 or +2. With GAS, the caregiver will create meaningful and relevant goals in collaboration with the patient. Secondly, these goals will be described at the International Classification of Functioning, Disability and Health (ICF) activity and participation level in accordance with the SMART (Specific, Measurable, Acceptable, Realistic and Time-specific) criteria [23]. After creating these individual goals, GAS scales have to be created by defining six realistic, distinct levels of outcome for -3, -2, -1, 0, +1 and +2, which will be used when evaluating progression during the rehabilitation. Patients in the intervention group preoperatively create their own rehabilitation goals, in collaboration with the selected and GAS-trained physiotherapist of their choice. Three goals will be set: one concerning a daily life activity, one concerning a work-related activity and one concerning a leisure time activity including sports which the patient wishes to perform better after KA. For these goals, GAS scales that can be used to objectify the progress in attaining these goals during follow-up will be created. Figure 2 shows an example of such a GAS scale.

**Fig. 2 Fig2:**
[figure not shown]
GAS scale

The multidisciplinary research team will check if the GAS goals and scaling seem to be realistic for that individual patient, taking into account relevant baseline characteristics like age, BMI, comorbidities, preoperative physical activity level (SQUASH) and level of anxiety (HADS). When consensus concerning the rehabilitation goals and GAS scales has been reached, the treating physiotherapist will create an individualized treatment protocol for that individual patient, in accordance with the physiotherapists of the research team. The duration of the rehabilitation protocol may vary across patients but is estimated to be between 3 and 12 months. After KA surgery, standard in-hospital treatment and initial PT rehabilitation will be followed in both treatment groups. After hospital discharge, the patient will follow his/her personalized rehabilitation protocol.

### Usual care physiotherapy rehabilitation

Patients of the control group will follow usual care physiotherapy according to the expert opinion of their treating physiotherapists. Results of our survey among physiotherapists in the area of the Amphia hospital show that ≥95 % of therapists generally work on pain reduction and the improvement of range-of-motion, muscle strength, endurance and gait pattern ([name] et al: Variable usual care rehabilitation and similar return to sports advice after knee arthroplasty: a survey amongst physiotherapists, submitted).

### Training of intervention physiotherapists performing GAS rehabilitation

Our multidisciplinary research team, consisting of two orthopaedic surgeons, two physiotherapists, a human movement scientist, a consultant for work-related musculoskeletal disorders and a researcher, followed an accredited course in GAS [24]. The research team will train the participating physiotherapists for the intervention group, which will be randomly selected (on a voluntary basis) from the group of physiotherapists that declared an interest in participating in the previous survey. Throughout the trial they will be guided and supervised by our multidisciplinary research team. To avoid selection bias, physiotherapists who treat patients from the intervention group will not treat patients from the control group and vice versa. In total, GAS-trained physiotherapists will be available at 25 physiotherapy locations where the intervention may take place. Another 30 locations have been selected where patients of the control group can follow usual care physiotherapy rehabilitation. Control group locations will also be randomly selected from the respondents to our previous survey.

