
### Data and statistical analysis

Analyses will be performed according to the intention-to-treat principle. In our power analyses, we accounted for 15 % loss to follow-up. Reasons for loss to follow-up will be explored. Patients’ baseline characteristics will be inspected to assess comparability between the two groups. Descriptive statistics will be presented for each group as the mean change (standard deviation, 95 % confidence intervals) in both primary and secondary outcomes from baseline to each time point, using IBM**®** SPPS software, version 19.0.

For our primary outcome measure, the VAS for activities, both mean postoperative values and mean differences between preoperative and postoperative values between intervention- and control groups will be compared. Our main outcome is the VAS score at twelve months postoperatively. Mixed-model statistics will be used to take into account the effects of time and treatment. Outcome will be presented as improvement of intervention group compared to control group, including 95 % confidence intervals. In the case of a positive treatment effect, additional information for reaching clinically relevant differences will be presented, such as number needed to treat (NNT) and absolute benefit increase (ABI).

For the analysis of the secondary outcomes KOOS, OKS – APQ, SQUASH, WORQ, NPS, PAM and HADS, both mean postoperative values (at diverse follow-up moments) and mean differences between preoperative and postoperative values between intervention- and control groups will be compared. Mann-Whitney U tests will be performed to compare total scores of these questionnaires between intervention- and control groups at the specified follow-up moments, namely at three, six and twelve months postoperatively.

Activ8® activity monitor data will be presented as the total amount of minutes per day spent on each activity. Differences in activity level between intervention- and control group, measured preoperatively and six months postoperatively, will be calculated using Mann-Whitney U tests. Finally, we will report on the GAS scores collected at three and six months postoperatively. GAS scores will be considered ordinal data and non-parametric analysis methods will be used. We will present the percentage of patients reaching their goals (0) as well as the percentage of patients reaching less than their goal (-1), more than their goal (+1) and far more than their goal (+2) [37].

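### Physiotherapists and locations are nested within arm, but the sample size makes no allowance for it and the stated analyses do not mention it; the effect is modest unless patients concentrate in few locations

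*Protocol article*

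**What the plan says.** Under Randomization and allocation concealment, patients are allocated individually, 1:1. Treatment is then delivered at sites that belong to one arm. The section on training of the intervention physiotherapists states: "In total, GAS-trained physiotherapists will be available at 25 physiotherapy locations where the intervention may take place". It adds 30 further locations for the control group and keeps the two sets of therapists apart: "physiotherapists who treat patients from the intervention group will not treat patients from the control group and vice versa".

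Under Sample size, the inputs are a difference of 10 points, an SD of 15, two-sided 5% significance and 90% power. This "results in a minimum of 98 participants, 49 in the intervention group and 49 in the control group", raised to 120 (60 per arm) for 15% dropout. No ICC, design effect or expected number of patients per location is given.

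Under Data and statistical analysis, the primary outcome is handled as follows: "Mixed-model statistics will be used to take into account the effects of time and treatment". Neither location nor therapist is named. Secondary questionnaire scores and Activ8 data are compared between arms by Mann-Whitney U tests.

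**The concern.** The therapist is part of the treatment in both arms. In the GAS arm the treating physiotherapist helps to set the goals and draws up the individual treatment plan (Intervention). In the control arm therapists treat by their own expert judgement (Usual care physiotherapy rehabilitation), and the Background reports that physiotherapists use widely differing methods. Some correlation between patients of the same location is therefore plausible.

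If every therapist treated patients of both arms, that shared variation would largely cancel in the comparison. Here it cannot, because no therapist serves both arms, so it stays in the variance of the treatment difference. An analysis that ignores it gives a standard error that is too small, an interval that is too narrow and a type I error above 5%. A sample size that ignores it has no margin set aside for it.

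**Working it through.** **Inputs from the protocol article.** Difference 10, SD 15, two-sided 5%, 90% power, 49 evaluable per arm, 60 enrolled per arm, 15% dropout (Sample size); 25 GAS and 30 control locations (Training section). **Assumptions, because the document gives no value:** ICC of 0.05 or 0.10; coefficient of variation (CV) of location size of 0 or 1.0; all locations in use.

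**1. Reproduce the plan's figure.** A two-sample t test with independent patients (noncentral t) gives power of 89.8% at 48 per arm and 90.4% at 49. So 49 per arm reproduces with a design effect of exactly 1. That the sample size assumes independence is thus shown by arithmetic.

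**2. Evaluable patients from 120.** 60 × 0.85 = 51 per arm. Without clustering, 51 per arm gives 91.5%, a small reserve above 90%.

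**3. Mean location size among evaluable patients.** 51/25 = 2.04 (GAS); 51/30 = 1.70 (control). Enrolled sizes (60/25 = 2.4 and 60/30 = 2.0) should not be paired with evaluable numbers: that would overstate the effect.

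**4. Design effect per arm.** DE = 1 + ((1 + CV²) × m − 1) × ICC, averaged over the two arms.
- ICC 0.05, CV 0: (1 + 1.04 × 0.05 = 1.052; 1 + 0.70 × 0.05 = 1.035), mean 1.04
- ICC 0.05, CV 1.0: (1 + 3.08 × 0.05 = 1.154; 1 + 2.40 × 0.05 = 1.120), mean 1.14
- ICC 0.10, CV 0: (1.104; 1.070), mean 1.09
- ICC 0.10, CV 1.0: (1.308; 1.240), mean 1.27

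**5. Consequences at 51 per arm.** The true standard error is √DE times the naive one. Type I error of the naive test is 2 × (1 − Φ(1.96/√DE)). Power is from the noncentral t with the variance multiplied by DE.

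| Assumed ICC | CV of size | DE | True SE vs naive | Type I error | Power |
|---|---|---|---|---|---|
| 0.05 | 0 | 1.04 | +2% | 5.5% | 90.4% |
| 0.05 | 1.0 | 1.14 | +7% | 6.6% | 87.8% |
| 0.10 | 0 | 1.09 | +4% | 6.0% | 89.2% |
| 0.10 | 1.0 | 1.27 | +13% | 8.2% | 84.0% |

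Taking degrees of freedom from the number of locations (25 + 30 − 2 = 53) lowers each power by a further half point or so.

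**6. If patients concentrate.** GAS patients choose their own trained physiotherapist, and 25 is the number of locations available, not the number that will be used. With only 10 equally used locations per arm, m = 5.1. ICC 0.05 then gives DE = 1 + 4.1 × 0.05 = 1.205, type I error 7.4% and power 86%. ICC 0.10 gives DE 1.41, 9.9% and 80%.

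**The case against.** The best counter-argument is that the clusters are tiny. With about two evaluable patients per location spread evenly, the planned 120 still gives 90.4% power at an ICC of 0.05. A reader might infer that the stated 90% power has been shown not to hold. It has not: the shortfall depends on an ICC and a spread of location sizes that the document does not give, and the rounding up to 120 absorbs some of it.

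Second, a mixed model is planned and its random effects are not listed. A condensed article may leave them to an analysis plan that is not shown, so it would go too far to say that the primary analysis certainly treats patients as independent. This stands for the primary outcome. It does not help the sample size, where independence is reproduced, or the secondary and Activ8 outcomes, where the named test has no place for a location effect.

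Third, the research team reviews goals and scales, agrees the treatment plans, and trains and supervises the GAS therapists. This may lower the correlation in that arm, but it does not apply to the 30 control locations, where care follows the therapist's judgement.

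Finally, a reader might infer that the results could not apply beyond these therapists. The document does not support that: therapists and control locations are to be randomly selected from survey respondents, though the intervention therapists are volunteers.

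**Conclusion.** The point holds in a limited form. Therapists are fully nested in arm, the sample size has no clustering allowance, the primary model as described names no location or therapist term, and the Mann-Whitney tests assume independent patients. For any positive ICC the direction is certain: intervals too narrow, type I error above 5%, power below the value for independent patients.

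The size is modest. With 51 evaluable per arm and all 55 locations used, type I error is 5.5-6.6% and power 90-88% at an assumed ICC of 0.05, and 6.0-8.2% and 89-84% at 0.10. The loss becomes material if patients gather in few locations, which the document leaves possible. None of this calls for more patients or makes the design invalid. It is a correction the plan should make, not one on which the trial depends.

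**What to change.** - **Primary outcome:** add a random intercept for physiotherapy location to the mixed model, with a small-sample degrees-of-freedom correction. Variances that differ by arm would be preferable in principle, but at about two patients per location they may not be estimable. Name the fallback in advance: one common variance, or cluster-robust standard errors.
- **Secondary outcomes and Activ8:** a Mann-Whitney test takes no random intercept. Use the same type of model, or a cluster-adjusted rank test, in its place.
- **Sample size:** keep 120. State that the 90% power assumes no clustering, and give about 88-90% under an assumed ICC of 0.05, together with the expected number of patients per location.

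No new data are needed: the physiotherapy evaluation questions under Outcome measures already record the location of physiotherapy. The cost is a slightly wider interval, a slightly lower stated power and a little more analysis work, since the secondary tests change as well. The choice should be fixed before outcomes are compared by arm, so that the standard error is not chosen afterwards.
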